## Abstract

As of September 30, 2015, a total of 1589 laboratory-confirmed cases of infection with the Middle East respiratory syndrome coronavirus (MERS-CoV) have been reported to the World Health Organization (WHO). At present there is no effective specific therapy against MERS-CoV. The use of convalescent plasma (CP) has been suggested as a potential therapy based on existing evidence from other viral infections. We aim to study the feasibility of CP therapy as well as its safety and clinical and laboratory effects in critically ill patients with MERS-CoV infection. We will also examine the pharmacokinetics of the MERS-CoV antibody response and viral load over the course of MERS-CoV infection. This study will inform a future randomized controlled trial that will examine the efficacy of CP therapy for MERS-CoV infection. In the CP collection phase, potential donors will be tested by the enzyme linked immunosorbent assay (ELISA) and the indirect fluorescent antibody (IFA) techniques for the presence of anti-MERS-CoV antibodies. Subjects with anti-MERS-CoV IFA titer of ≥1:160 and no clinical or laboratory evidence of MERS-CoV infection will be screened for eligibility for plasma donation according to standard donation criteria. In the CP therapy phase, 20 consecutive critically ill patients admitted to intensive care unit with laboratory-confirmed MERS-CoV infection will be enrolled and each will receive 2 units of CP. Post enrollment, patients will be followed for clinical and laboratory outcomes that include anti-MERS-CoV antibodies and viral load. This protocol was developed collaboratively by King Abdullah International Medical Research Center (KAIMRC), Gulf Cooperation Council (GCC) Infection Control Center Group and the World Health Organization—International Severe Acute Respiratory and Emerging Infection Consortium (ISARIC-WHO) MERS-CoV Working Group. It was approved in June 2014 by the Ministry of the National Guard Health Affairs Institutional Review Board (IRB). A data safety monitoring board (DSMB) was formulated. The study is registered at http://www.clinicaltrials.gov (NCT02190799).

## Background

The Middle East respiratory syndrome coronavirus (MERS-CoV) was initially identified in September 2012 from samples obtained from a Saudi Arabian patient who developed severe acute respiratory infection and subsequent acute renal failure leading to death (Zaki et al. 2012). As of September 30, 2015, a total of 1589 cases have been identified with 567 related deaths (World Health Orgnization 2015). To date, there is no specific treatment of proven effect for MERS-CoV infection. Public Health England and the International Severe Acute Respiratory and Emerging Infection Consortium (ISARIC) have published a decision support tool for clinicians managing cases of MERS-CoV infection. The document suggests that current evidence is strongest for testing convalescent plasma (CP) or other therapeutics which contain neutralizing antibodies (such as hyperimmune immunoglobulin) for treatment of serious MERS-CoV illness (Public Health England 2015). Prior experience in SARS and severe influenza suggest that CP may be considered for patients who are deteriorating (despite other specific and supportive therapy) and in whom the virus remains detectable (Hung et al. 2011; Luke et al. 2006; Cheng et al. 2005; Kong and Zhou 2006; Yeh et al. 2005). A recent systematic review of 32 reports from SARS and severe influenza concluded that CP therapy appears safe and may reduce mortality, especially if administered early in the illness (Mair-Jenkins et al. 2015). An exploratory post hoc meta-analysis showed a statistically significant reduction in the pooled odds of mortality following treatment compared to placebo or no therapy (odds ratio 0.25; 95 % confidence interval 0.14–0.45; I^2^ = 0 %) (Mair-Jenkins et al. 2015). Citing case series, the authors commented that (1) patients with severe presentations appeared to demonstrate temporal clinical improvements after treatment with CP and (2) administration as early as possible in the diseases course appears to be associated with greatest potential clinical effect. One randomized clinical trial (RCT) in critically ill influenza A (H1N1pdm09)-infected patients found a survival benefit when hyperimmune globulin was administered within 5 days of symptom onset (Hung et al. 2013).

However, there are no data at present to support the efficacy of CP treatment in MERS-CoV infection; therefore, it has been recommended to administer CP only in the context of a clinical trial. While an RCT will be required to evaluate effectiveness, evaluating effectiveness on clinical endpoints such as mortality will likely require several hundred to several thousand seriously ill MERS-CoV patients in order to achieve sufficient statistical power, anticipating reasonable potential effect sizes. Additionally, CP from different MERS-CoV survivors will likely contain differing levels of neutralizing anti-MERS-CoV antibodies. Since seriously ill MERS-CoV-infected patients may have detectable viral RNA in various locations that can be sampled (for example lower respiratory tract secretions) for prolonged periods, it might be possible to first determine the relationship between neutralizing antibody dose and antiviral effects on clinical and laboratory features in a small open-label study. This information would be very helpful to design of an RCT and in determining the most appropriate neutralizing antibody dose, or dosing range for the study. This may also inform dose selection for follow-on anti-MERS-CoV antibody preparations currently in pre-clinical development (for example, neutralizing human monoclonal antibodies, polyclonal human neutralizing immunoglobulin derived from transchromosomic cattle (personal communication, [name]).

Therefore, we plan to conduct a 2-phase study. In the first phase (CP collection phase), we will explore the feasibility of collection of CP from donors who have significant titers of anti-MERS-CoV antibodies. In the second phase, patients with MERS-CoV infection will be treated with CP. If the protocol is feasible, safe, and associated with temporal changes in viral load and illness, this pilot study will inform a larger concealed intervention, placebo-controlled RCT that is powered to evaluate efficacy of CP on relevant clinical outcomes.

## Methods

### Study population

#### CP collection phase

The inclusion criteria for screening potential CP donors include individuals from the following cohorts: (1) healthcare workers (HCWs) who had documented exposure to MERS-CoV, (2) recovering patients from confirmed or suspected MERS-CoV infection, (3) household contacts of known MERS-CoV infected patients and (4) other subjects who are willing to donate plasma. Females with prior pregnancy will not be included for donation.

#### CP therapy phase

We will screen consecutive critically ill patients admitted to the intensive care unit or other areas of the hospital where critically ill patients receive care for the following criteria:

Inclusion criteriaCritical illness as defined by one or more of the following: admission to an ICU; current receipt of mechanical invasive or non-invasive ventilation; partial pressure of oxygen to fraction of inspired oxygen ratio (PaO2:FiO2) of <300 mmHg; current receipt of intravenous vasoactive medications to maintain mean arterial pressure >65 mmHg; new-onset (since development of MERS-CoV symptoms) receipt of renal replacement therapy or extra-corporeal life support.Laboratory-confirmed MERS-CoV infection (by real-time reverse-transcription polymerase chain reaction rRT-PCR).Age of more than or equal to 14 years.

Exclusion criteriaSymptomatic illness exceeding two weeks (14 days) at time of enrollment.Negative rRT-PCR from respiratory secretions or blood within 48 h prior to assessment of eligibility.History of allergic reaction to blood or plasma products (as judged by the investigator).Known IgA deficiency.Medical conditions in which receipt of 500 mL intravascular volume may be detrimental to the patient (e.g., actively decompensated congestive heart failure).

#### Informed consent

The research coordinator and/or physician investigator will explain the objectives of this study and its potential risks and benefits to the donor or patient (or to his/her surrogate decision maker) and will obtain the following consent forms in and as appropriate:

CP collection phaseConsent for MERS-CoV serologic testing and MERS-CoV RT-PCR for donors.Consent for CP donation for those who have elevated anti-MERS-CoV titers as described below.

CP therapy phaseConsent for enrollment in the CP therapy phase.Consent for enrollment in the observational study where NO intervention will be received, but participants will still have blood (and possibly respiratory) samples taken—for participants not receiving the intervention.

### Study procedures

#### For the CP collection phase

Eligible candidates for CP donation (as per the inclusion and exclusion criteria above) will be approached to have their blood tested for anti-MERS-CoV serology (see laboratory methods). Subjects who are seropositive will be screened subsequently for MERS-CoV rRT-PCR to exclude active infection.Subjects with anti-MERS-CoV-specific titer ≥1:160 and no clinical (not requiring medical support for respiratory or other organ function) or laboratory (rRT-PCR negative) evidence of MERS-CoV infection will be screened for eligibility for plasma donation according to the standard criteria in accordance with the WHO Guidelines Assessing Donor Suitability for Blood Donation (The World Health Organization 2015).Those who meet the plasma donation criteria will be invited for donation according to the WHO Blood Regulators Network (BRN) Position Paper on Collection and use of convalescent plasma or serum as an element in Middle East respiratory syndrome coronavirus response (WHO Blood Regulators Network (BRN) 2015). Plasma may be collected by apheresis as frequently as twice every month, as appropriate for the individual donor. Collection will be performed by trained blood bank staff operating under the standard operating procedures in certified facilities. The collected frozen plasma will be stored in the blood bank after being tested for serology of hepatitis B and C viruses (HBV and HCV), human immunodeficiency virus (HIV), malaria, syphilis and human T-lymphotropic virus (HTLV) types I and II and nucleic acid testing (NAT) for HBV, HCV and HIV according to international guidelines.

#### For the CP therapy phase

Critically ill MERS-CoV patients who meet the above patient eligibility criteria will be approached for consent.Patients will have their blood type determined. CP must be ABO compatible with the recipient’s blood type.The trial intervention include the administration of 2 units of CP. Each unit of plasma will be given over 2 h with an interval of 1 h between the two units. Plasma transfusion will be done in accordance with the standard policies for administration of blood products.

#### Co-interventions

The clinical team will have full, independent control of patient management and as such, management other than CP therapy will not be influenced by the intervention or study team. Co-interventions, including corticosteroids, ribavirin, intravenous immunoglobulin and interferon, will be documented on the study case report forms.

#### Co-enrollment

Co-enrollment in another study is permissible as long as the enrollment in the other study would not be at moderate to high risk of biologically or analytically confounding the results of this study, as judged by the study management committee and as per the published guidelines.

#### Frequency and duration of follow-up

Clinical and laboratory data will be collected at baseline, 30 min after first dose, 30 min after second dose, study days 1, 3, 5, 7, 14, and 28.

### Outcome measures

#### CP collection phase

We will explore the feasibility of the study intervention, as measured by ability to screen potential plasma donors, and derive sufficient plasma to enrol 20 patients in a 12 months period. We will also qualitatively describe logistical challenges experienced through the conduct of this study, including ethical, administrative and regulatory challenges.

#### CP therapy phase

We will establish safety of the study intervention, as measured by number of serious adverse events related to study intervention (adverse events include development of complications of intravascular volume overload and clinical pulmonary edema by temporally related-shortness of breath, chest radiograph findings and change in oxygenation requirements; development of transfusion-related acute lung injury (TRALI) or substantial allergy or anaphylaxis). These serious events will be adjudicated by a committee of 3 investigators.*Clinical Outcomes* We will measure (1) sequential organ failure assessment (SOFA) scores on study days 1, 3, 5, 7, 14, and 28 (2) requirement for organ support (oxygen and ventilation; dialysis; vasopressors) after enrollment; (3) length of stay in ICU defined as the number of calendar days between admission and final discharge from ICU for the same ICU admission of enrollment; and duration of mechanical ventilation, defined as the number of calendar days between start and final liberation from mechanical ventilation for the same ICU admission of enrollment and hospital length of stay as defined as the number of calendar days between admission to hospital and final discharge from hospital for the same hospital admission; and (4) vital outcome (mortality) in ICU, hospital and at 28 days.Other clinical outcomes include “ICU-free days”, defined as the number of days that patients are not in ICU in the first 28 days after enrollment. Patients who die within 28 days will be counted separately, and not categorised by ICU-free days. Similarly, “ventilator-free days” is defined as the number of days that patients do not receive mechanical ventilation in the first 28 days after enrollment. “Renal replacement therapy-free days” and “vasopressor-free days” are defined in a similar way. Serial chest radiograph findings, as obtained by the clinical team will also be recording as per case report form, graded as unilateral or bilateral infiltrates, in 1–4 quadrants.*Laboratory Outcomes* We will measure the following laboratory outcomes:The serum level of anti-MERS-CoV antibodies before and after administration of CP.MERS-CoV viral load (the primary laboratory outcome is viral clearance from all sampled sites by day 3 after administration of CP).

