### Statistical and analytical plan

#### Sample size calculation

This is an exploratory study, aimed at rectifying the current lack of information on the use of CP to treat MERS-CoV infection. Due to the exploratory nature of this study and the paucity of sequential data on viral RNA levels in respiratory tract and blood samples from MERS-CoV-infected patients, and on their clinical progress, the sample size is fixed at 20, which is a realistic target for a study of 12 months duration. The sample size of 20 is sufficient to reach a conclusion that the 28-day survival rate significantly exceeds 60 % (p = 0.032, 2-sided) if 17 or more patients survive for the 28 days of follow-up. This would represent promising evidence to motivate a full-scale comparative clinical trial.

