### Statistical analyses

#### Analysis of viral load data

Serial MERS-CoV viral load measurements will be displayed as box and whisker plots for the 20 treated patients against time.The probability of a patient having an undetectable viral load from all sampled sites by day 3 after administration of therapy will be estimated by the proportion of the 20 treated patients for whom this occurs. An exact, conservative, two-sided confidence interval for this probability will be calculated using the method of Clopper and Pearson (1934).The relationship between log viral load at day 3 and the neutralizing antibody dose received will be characterised by fitting a regression model to the data from the 20 treated patients. The log viral load at baseline will be included in this model.The relationship between the probability of a patient having an undetectable viral load by day 3 and the neutralizing antibody dose received will be characterised by fitting a log-logistic regression model to the data from the 20 treated patients. The log viral load at baseline will be included in this model.

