#### Analysis of clinical data

The SOFA score and indicators of whether the patient requires organ support via oxygen and ventilation, dialysis or vasopressors will be plotted against time.The relationships between the SOFA score at day 3 and the neutralizing antibody dose received, and between receipt of any type of organ support during the 28 days of observation and the neutralizing antibody dose received, will be characterised by fitting a logistic regression model to the data from the 20 treated patients. The log viral load at baseline will be included in these models.The vital status (alive or dead) of each patient will be recorded for all days 0–28. The proportion alive will be plotted against time.The relationship between the hazard of death and the neutralizing antibody dose received will be characterised by fitting a Cox proportional hazards regression model to the data from the 20 treated patients. The log viral load at baseline will be included in this model.The probability of a patient dying on or before 28 days will be estimated by the proportion of the 20 treated patients for whom this occurs. An exact, conservative, two-sided confidence interval for this probability will be calculated using the method of Clopper and Pearson (1934).The time from infection/exposure and sample collection in days, duration from infection/exposure to CP therapy, length of stay in ICU; the number of ICU-free days; the duration of mechanical ventilation; the numbers of ventilator-free days, of renal replacement therapy-free days, and of vasopressor-free days; and the length of stay in hospital will be presented as histograms, and suitable summary statistics will be computed.

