### Discussion and current status

This protocol was developed collaboratively by King Abdullah International Medical Research Center (KAIMRC), Gulf Cooperation Council (GCC) Infection Control Center Group and the World Health Organization—International Severe Acute Respiratory and Emerging Infection Consortium (ISARIC-WHO) MERS-CoV Working Group. It was approved by the Ministry of the National Guard Health Affairs Institutional Review Board (IRB) (approval number IRBC/13/244, 5th June 18, 2014) and has been registered at clinicaltrials.gov (NCT02190799).

If proven effective, CP therapy is an attractive therapeutic option for MERS-CoV infection. Besides the biologic plausibility of this therapy, it is easy to obtain and administer, relatively inexpensive, and is likely to be acceptable to patients and treating teams. Side effects are unlikely to differ from those of transfusion of any other fresh frozen plasma. We believe this study protocol sets the stage to a large efficacy trial.

The strengths and weaknesses of the study protocol should be noted. In the CP collection phase subjects will be enrolled from 4 different cohorts, in order to explore all potential donors. It is unknown, at this point, which subjects are likely to have high antibody titers and therefore be CP donors. We are hoping that this feasibility study will help identifying a group of superdonors who have very high titers. By identifying the characteristics of such individuals, a more focused approach for donation can be followed. The CP therapy phase is not designed to establish efficacy; such objective requires an adequately powered randomized controlled trial. However, we believe performing this feasibility study is an essential step to examine the safety, clinical and laboratory effects and the pharmacokinetics of the MERS-CoV antibody response. The study involves giving critically ill patients this therapy in a controlled monitored setting. However, a recent systematic review suggested that early treatment with CP is likely to be more effective than late treatment (Mair-Jenkins et al. 2015). Therefore, if the feasibility study shows that CP is safe and feasible, the next step should be a randomized controlled trial that is sufficiently powered to detect effect on mortality and enrolls patients early in the course of the disease.

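### The therapy phase promises to establish safety from a count of related serious adverse events, but 20 single-arm patients can only estimate that rate

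*Protocol article*

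**What the plan says.** Safety is the first outcome listed for the therapy phase (Outcome measures, CP therapy phase): "We will establish safety of the study intervention, as measured by number of serious adverse events related to study intervention". The same paragraph names the expected types of event and adds: "These serious events will be adjudicated by a committee of 3 investigators".

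Two sections tie safety to the next trial. The Background sets three joint conditions for the pilot to inform a larger trial: "If the protocol is feasible, safe, and associated with temporal changes in viral load and illness". The Discussion is more direct: "if the feasibility study shows that CP is safe and feasible, the next step should be a randomized controlled trial".

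The number of patients was not chosen for safety. Under Sample size calculation, "the sample size is fixed at 20, which is a realistic target for a study of 12 months duration", and the only supporting figure concerns 28-day survival.

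For two other binary outcomes, undetectable virus by day 3 and death by 28 days, the article defines the proportion of the 20 treated patients and adds: "An exact, conservative, two-sided confidence interval for this probability will be calculated using the method of Clopper and Pearson (1934". The article sets out no corresponding proportion for safety.

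**The concern.** To establish safety is to rule out a level of harm that would matter. The article names no such level, and a single-arm group of 20 leaves a wide range of related-event rates open even in the best case. The stated objective thus claims a property that the design does not have.

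The article is also uneven on this. The Abstract speaks of studying safety and the Discussion of examining it. For efficacy the Discussion says that the phase was not built to establish it and leaves that to an adequately powered randomised trial. The same restraint is missing from the safety objective.

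The measure adds a smaller difficulty. It is a number of events, whereas the risk that a later trial needs to know is the share of patients affected. Three events in one patient and one event in each of three patients give the same total but different risks.

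At stake is what the trial may conclude. A low count could be reported as safety established and carried into the case for the larger trial, without a statement of how much harm remains compatible with the data.

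**Working it through.** **Inputs**
- n = 20 treated patients (Sample size calculation).
- Interval method: exact two-sided Clopper-Pearson, as planned for viral clearance and 28-day death (Statistical analyses).
- Confidence level: not stated in the article. I assume 95% and show the effect of other levels.
- Acceptable related-event rate: none is given. The 5% and 10% rates below are my illustrations only.

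**The plan's own figure.** The sample size section gives a two-sided p = 0.032 for 17 or more survivors of 20 against 60% survival. The exact binomial tail is P(X ≥ 17 | 20, 0.60) = 0.01596, and doubled it is 0.0319. The figure reproduces, but it concerns survival. There is no safety figure to reproduce.

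**No patient with a related serious event (0/20).** The lower limit is 0. The upper limit p solves (1 − p)^20 = 0.025, so p = 1 − 0.025^(1/20) = 0.168.

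**One patient (1/20).** Lower limit: 1 − 0.975^(1/20) = 0.0013. Upper limit: (1 − p)^20 + 20p(1 − p)^19 = 0.025 gives p = 0.249.

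**Two and three patients**, by the same method from beta quantiles:

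| Patients with a related event | Two-sided 95% limits |
|---|---|
| 0/20 | 0 to 16.8% |
| 1/20 | 0.1% to 24.9% |
| 2/20 | 1.2% to 31.7% |
| 3/20 | 3.2% to 37.9% |

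**Sensitivity to the assumed level, for 0/20.** A one-sided 95% limit (equal to a two-sided 90% limit) is 1 − 0.05^(1/20) = 13.9%. A two-sided 99% limit is 1 − 0.005^(1/20) = 23.3%. The conclusion is the same at each level.

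**Chance of seeing nothing.** At an illustrative true rate of 5%, P(0 of 20) = 0.95^20 = 0.36. At 10% it is 0.90^20 = 0.12.

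**Events against patients.** A total of three events is compatible with 1/20 (0.1% to 24.9%) or with 3/20 (3.2% to 37.9%). The total alone does not say which.

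**The case against.** The best defence is that this is one strong verb in an otherwise modest document. The sample size section calls the study exploratory, and the Abstract and Discussion use softer terms for safety. Events are adjudicated, and an independent DSMB may recommend termination. Organ function, organ support and mortality are followed too. The Background cites a systematic review in which the therapy appeared safe in other infections, and the Discussion expects side effects like those of ordinary plasma. Any pilot of 20 has limits of this width.

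Most of that stands, and it bounds the point. A reader might infer several stronger things that the article does not support:
- *That zero or one related event would count as safe.* No such rule is written, and no threshold is set.
- *That safety rests on a bare count.* Adjudication and DSMB review are both described.
- *That the missing interval is itself a fault.* An analysis plan that is not shown may well supply it, so its absence is not the point.
- *That patient-level information would be lost.* Nothing prevents events being listed by patient.
- *That 20 patients are too few to go on to a randomised trial.* Excluding rates above about 17% may be enough for a monitored trial, provided this is said openly.

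What the defence does not remove is the objective as stated. Adjudication and oversight do not narrow the interval. External experience may make safety plausible, but it does not let this trial establish it. An interval added in an analysis plan would leave the objective, and the Discussion's reliance on a showing of safety, unchanged.

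**Conclusion.** The point holds in limited form. The safety objective overstates what 20 single-arm patients can show and is out of line with the article's own wording elsewhere, including its restraint on efficacy. In the most favourable case, 0/20, a related-event rate of up to 16.8% remains compatible with the data, and with 1/20 up to 24.9%.

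These limits assume a 95% level and a patient-level count out of 20. They do not depend on the illustrative 5% and 10% rates. No figure in the article is wrong, and the size of the pilot is not in question. Severity is minor to moderate: the change affects what the trial may conclude about safety, not how it is run.

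**What to change.** 1. In the therapy-phase outcome section, replace the aim of establishing safety with that of estimating the rate of related serious adverse events.
2. Make the measure the number of the 20 treated patients with at least one serious adverse event adjudicated as related. List the total number of events as a secondary line.
3. Report that proportion with the Clopper-Pearson interval already planned for viral clearance and 28-day death, and state the confidence level.
4. In the outcome section and in the Discussion, say that zero events in 20 would exclude only rates above about 17% (at 95%), so that a statement of safety is read in that sense.

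The cost is some rewording and one more exact interval, with no extra patients or data. Adjudication and DSMB oversight stay as they are. The downside is a less favourable safety statement, though one that the data can support.

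### 28-day survival is estimated only in treated patients from an unstated day 0, so deaths between consent and infusion would drop out and survival can be inflated against the 60% reference

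*Protocol article*

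**What the plan says.** **Time origins.** Under Outcome measures (CP therapy phase), ICU-free days are counted "in the first 28 days after enrollment", and the ventilator-, dialysis- and vasopressor-free days follow the same pattern. The same section counts the primary laboratory outcome, viral clearance by day 3, from administration of plasma. ICU stay runs from admission: "the number of calendar days between admission and final discharge from ICU for the same ICU admission of enrollment". For 28-day mortality no origin is given there. Analysis of clinical data records vital status on days 0 to 28 without saying what happens on day 0.

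**Analysis set.** Analysis of clinical data has the probability of "dying on or before 28 days will be estimated by the proportion of the 20 treated patients", and fits the Cox model to the same 20.

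**Decision figure.** Sample size calculation states that 20 patients suffice to conclude that the "28-day survival rate significantly exceeds 60"% "if 17 or more patients survive for the 28 days of follow-up", with a two-sided p of 0.032. It regards this as promising evidence for a comparative trial. It does not say where the 60% comes from or from what moment it is counted.

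**Steps before infusion.** Study procedures (For the CP therapy phase) puts consent first, then blood typing, and adds that "CP must be ABO compatible with the recipient"'s blood type. Informed consent provides a separate observational consent "for participants not receiving the intervention".

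**The concern.** A patient becomes one of the treated 20 only by living until the infusion and by having compatible plasma available. Suppose survival, or the 60% it is compared with, is counted from enrolment. The days between enrolment and infusion are then days on which no treated patient can have died. Someone consented for plasma who dies in that interval is not a treated patient, and no part of the article says how that person is counted or whether a replacement is enrolled.

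An omitted pre-infusion death can only raise the survival proportion. At stake is the 17-of-20 mark, the one figure that the article ties to a decision on a full-scale trial. The mark has no slack: 17 is the smallest count that passes.

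**Working it through.** **Inputs from the article**
- n = 20, reference 28-day survival 0.60, success at 17 or more survivors, stated two-sided p = 0.032 (Sample size calculation).
- Estimate and Cox model restricted to treated patients (Analysis of clinical data).

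**Inputs not in the article, assumed here**
- The wait w from enrolment to infusion: 0.5 to 3 days.
- The hazard of death: constant over the 28 days, with 60% alive at day 28 from enrolment and no effect of plasma.
- Patients who die before infusion are replaced, so that 20 are treated.

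**Step 1. Reproduce the stated figure.** With X binomial (20, 0.60):

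P(X ≥ 17) = 0.01235 + 0.00309 + 0.00049 + 0.00004 = 0.0160 after rounding (0.01596 unrounded).

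Doubled, this is 0.0319, the stated 0.032. For 16 survivors the doubled tail is 0.102, so 17 is the correct cut-off.

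**Step 2. Survival counted from enrolment, treated patients only.** Under a constant hazard, S(w) = 0.60^(w/28). Survival to day 28 among those who reach infusion is 0.60 / S(w) = 0.60^(1 − w/28).

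| Wait (days) | Die before infusion | Apparent 28-day survival | P(17 or more of 20) |
|---|---|---|---|
| 0 | 0% | 60.0% | 1.6% |
| 0.5 | 0.9% | 60.5% | 1.8% |
| 1 | 1.8% | 61.1% | 2.0% |
| 2 | 3.6% | 62.2% | 2.6% |
| 3 | 5.3% | 63.4% | 3.2% |

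**Step 3. The same question without a hazard model.** Let q be the share who die before infusion. Survival among the treated is 0.60 / (1 − q). For q = 2%, 5% and 10% this is 61.2%, 63.2% and 66.7%, and P(17 or more of 20) is 2.1%, 3.1% and 6.0%.

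**Step 4. Effect on one observed result.** Let 17 of 20 treated patients survive, and let k further patients consented for plasma have died before infusion. Counting all of them, the doubled exact tail against 0.60 is:

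| k | Survivors / counted | Survival | Doubled exact p |
|---|---|---|---|
| 0 | 17/20 | 85.0% | 0.032 |
| 1 | 17/21 | 81.0% | 0.074 |
| 2 | 17/22 | 77.3% | 0.144 |

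**Step 5. Does moving day 0 to infusion suffice?** Under a constant hazard it does: 28-day survival from infusion is again 60%. If mortality is concentrated early it does not, unless the 60% is counted from the same point. Take an extreme case with a Weibull hazard of shape 0.5 scaled to 60% at day 28 and a 3-day wait. The chance of 17 or more is 12.4% counted from enrolment and still 9.2% counted from infusion. Both the shape and the wait are assumptions here. The example shows only that the origin of the 60% must be stated as well.

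**The case against.** The strongest reply is that the wait may be negligible. The list under Frequency and duration of follow-up puts both doses between baseline and study day 1, and clearance by day 3 after plasma is evidently read at study day 3. Study days therefore look as if they start at infusion, and day 28 in the same list would be the survival endpoint. Collected plasma is stored frozen. The Abstract plans for 20 patients to be enrolled and each to be treated, so enrolled and treated coincide by intention. The study is exploratory, and its Discussion says the therapy phase is not designed to establish efficacy.

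Much of this stands. A half-day wait at constant hazard moves 1.6% only to 1.8%. It does not settle the point, though. The schedule suggests an origin but does not state one, and the free-day definitions use a different one. The Abstract states an intention and does not say how a consented patient who is never infused is counted. An origin at infusion also does not align the 60%, whose origin is open.

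Two stronger readings are tempting. A reader might infer that pre-infusion deaths do vanish and that survival is inflated. The documents do not support this: they give neither a delay nor a death rate before infusion, and nowhere say that such patients are dropped or replaced. A reader might also infer that the mixed clocks are themselves the source of bias. They are not. Clearance from infusion and ICU stay from admission are natural descriptive definitions, and neither enters the 17-of-20 comparison. The risk comes from a treated-only set combined with an unstated survival origin.

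**Conclusion.** The point holds as a conditional risk. As written, a patient consented for plasma who dies or finds no compatible plasma before infusion would be outside the survival estimate. Any deaths lost this way make 28-day survival look better against 60%.

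The size cannot be derived from the documents. With no pre-infusion deaths it is zero. With no plasma effect, a constant hazard and an assumed wait of 0.5 to 3 days, the chance of reaching 17 of 20 is 1.8% to 3.2% instead of 1.6%. The sharper consequence is fragility: a single uncounted death turns a two-sided p of 0.032 into 0.074. The stated 0.032 is itself computed correctly. The matter deserves correction because the figure is meant to support the decision on a larger trial, and because the correction is a matter of wording.

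**What to change.** 1. In Outcome measures, Sample size calculation and Analysis of clinical data, define day 0 for the treated set as the start of the first plasma unit. Apply it to 28-day survival, the Cox model, SOFA and the free-day outcomes, as is already done for clearance.
2. State the time origin and the source population of the 60% reference, and make them match that day 0.
3. Beside the 17-of-20 result, report 28-day survival from enrolment for every patient consented to the therapy phase, with the number who died before infusion or were not infused for another reason. This also serves the feasibility aim.

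ICU stay and duration of ventilation can stay as defined.

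The cost is a few sentences, plus enrolment and infusion dates and 28-day vital status for the patients who were not infused. The downside is that the companion survival figure may be slightly less favourable than the treated-only one.
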